#### Syndemic outcome

The syndemic outcome is self-reported health at phase 3 (very good, good versus fair, bad, very bad).

#### Syndemic constructs

Syndemic constructs include social adversity (socioeconomic adversity and adverse childhood experiences; ACEs) and mental, physical and oral multimorbidity.

Socioeconomic adversity will be measured by SEP indicators at individual, household and neighbourhood (area) levels: free school meals, car/van ownership, home ownership, parental (household) employment status and household overcrowding. Household employment status will be measured using the “dominance approach”, assigning the household the employment status of the parent/carer with the higher status.

ACEs will be measured by experiences of repeated bullying in school (“sometimes”, “about once a week” or “several times a week” versus “never bullied”, “I have not been bullied in school this term” or “once or twice”), lack of parent/carer involvement; experiences of parents often arguing or fighting; being looked after; continuing family money problems; close family dying; and home suffering damp, mould, vibration, noise from neighbours, cold, road traffic noise or dust.

Mental multimorbidity will include depression and having mental health problems. The former is measured by the Short Moods and Feelings Questionnaire (where a sore of ≥ 8 is indicative of depression). The latter is measured by the Strength and Difficulties Questionnaire (where a score of ≥ 17.5 is indicative of having mental health problems) (29).

Physical multimorbidity will be measured by having chronic illness (asthma, eczema, epilepsy, diabetes, hearing problems, eyesight problems, hay fever, chronic fatigue syndrome/ME or other chronic illness).

Oral multimorbidity will include the number of decayed teeth (as a continuous and categorical variable) and presence of toothache.

#### Mediators

Mediators are health behaviours and lifestyle. No data is available in RELACHS on C reactive protein or other inflammatory markers.

Health behaviours and lifestyle variables will include being overweight or obese (having BMI above the 85th percentile and 95th percentile, respectively); alcohol consumption (never tried versus tried alcohol or consumed alcohol in the past week), smoking (never smoked versus ever tried or regular smoker), drug use (never tried versus tried drugs: cannabis, glue/solvents/gas, ecstasy, crack, heroin, amphetamines, LSD, cocaine and/or khat), physical activity (active versus inactive, exercising more or less than twice a week for an hour), diet as measured by the frequency of consumption of breakfast, crisps/savoury snacks, sweets, biscuits, fried food and fizzy drinks (“never”, “hardly ever”, “1-2 days a week” versus “3-4 days a week” or “daily”) as well as daily consumed portions of fruits and vegetables (5 or more portions daily versus less than 5 portions daily or none); dieting behaviour as measured by ever dieted to lose weight (Yes versus No) as well as present attempts to diet to lose or gain weight (Yes versus No); and tooth brushing (twice daily versus less than twice daily).

#### Covariates

Covariates are demographic variables: age, sex and ethnicity.

#### Statistical analysis

Descriptive statistics will be used to summarise participants characteristics. For NHANES and RELACHS data, survey analysis procedures will be used to account for the sample weights, stratification and clustering of the complex sampling design to ensure representative estimates.

To answer the research questions on the presence of syndemic relationships, a structural equation modelling (SEM) technique will be utilised to conceptualise syndemic constructs and model complex relationships between directly observed and indirectly observed (latent) variables. The SEM technique has gained increasing popularity in syndemic research (30, 31). To use this technique, the following steps will be undertaken:

In step one, exploratory and confirmatory factor analyses will be used to identify the clustering nature and reduce the number of indicators (observed variables) under each theoretical construct. In step two, a SEM to predict premature mortality and all-cause hospitalisation, controlling for age, sex and ethnicity, will be run. Analysis will include identifying whether the indicators chosen to measure the latent constructs are acceptable. confirmatory factor analysis will be used to provide information on how indicator items measure underlying (latent) constructs. In step three of the analysis, SEM will be used to examine the direct and indirect relationships between the constructs. The goodness of fit (GoF) of the SEM model to the data will be assessed considering the indices of Comparative Fit Index (CFI) and Tucker-Lewis Index (TLI; where values >.90 indicate a good fit), root mean square error of approximation (RMSEA), and Standardised Root Mean Square Residual (SRMR; where value <.05 indicate a good fit). In step four, the synergistic (multiplicative) interactions between different latent constructs and measured variables will be tested using two-step estimation procedures (32).

To answer the question on whether syndemic relationships vary by age, sex and ethnicity, stratified analyses by age, sex and ethnicity will be performed.

Full Information Maximum Likelihood technique will be used as a pragmatic approach for data missing estimation for SEMs. This approach produces unbiased parameter estimates and standards errors (33). For UK BioBank and RELACHS datasets, stability of exposure data over time will be checked by calculating the intraclass correlation coefficients between baseline and follow up data.

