## Introduction

The relationship between social adversity and mental, physical and oral multimorbidity is a topical yet under-researched area. A recent critical review proposed that such relationship is likely to form a syndemic (1). The review built its argument on the fact that mental disorders, physical multimorbidity and oral diseases share the same social determinants and have bidirectional relationships that are likely to have synergistic effects in terms premature mortality and excessive burden of morbidity (1–4).

Syndemics are defined as “the aggregation of two or more diseases or other health conditions in a population in which there is some level of deleterious biological or behaviour interface that exacerbates the negative health effects of any or all of the diseases involved” (5). Such adverse disease interactions can occur amongst all types of diseases infectious or non-communicable. They emerge in populations that experience social adversities such as poverty, stigmatisation, systemic discrimination and violence.

Though used interchangeably to describe the co-existence of multiple conditions in any given population, the syndemics concept goes beyond the concepts of comorbidity and multimorbidity. ‘Comorbidity’ describes the co-occurrence of additional conditions alongside a primary ‘index’ condition (6). ‘Multimorbidity’ refers to several conditions that co-exist in tandem but there is no single focus of attention on one condition over the others (7). However, ‘syndemics’ emphasise the adverse interaction between co-occurring diseases (bio-bio interaction) and underscore the role of precipitating and perpetuating adverse social, economic, environmental, political and healthcare contextual factors. These factors cluster with the myriad of diseases and shape their interaction (bio-social interaction) (8). Both types of interaction (bio-bio and bio-social) should exist to form a syndemic. The nature of these interactions should be “synergistic” rather than “additive”; meaning that the produced disease burdens are far more than the sum of disease burdens of each condition or factor alone. A few studies have operationalised the above syndemic concept correctly (8, 9).

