#### Syndemic outcomes

The syndemic outcomes are premature mortality and all-cause hospitalisation. Mortality data are obtained from the death register based on death certificates held within the NHS Digital (England and Wales) and the NHS Central Register (Scotland) between 01/01/2011 and 30/09/2021. All-cause hospitalisation data are obtained from the Hospital Episode Statistics data - Admitted Patient Care (England), Scottish Morbidity Records – General / Acute Inpatient and Day Case Admissions (Scotland), and Patient Episode Database (Wales) between 01/01/2011 and 28/02/2018.

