#### Syndemic outcomes

The syndemic outcomes are premature mortality and all-cause hospitalisation. Mortality data are obtained from the National Death Index (available up to 31 December 2015). All-cause hospitalisation data are based on being hospitalised in the year preceding the survey.

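### The Introduction defines synergy as burden beyond the sum, but step four tests only multiplicative interaction, so the syndemic conclusion can be wrong in either direction

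*Protocol article*

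**What the plan says.** The Protocol article's Introduction separates a syndemic from comorbidity and multimorbidity by the kind of interaction involved. The interaction must go beyond additivity: "the produced disease burdens are far more than the sum of disease burdens of each condition or factor alone". It also makes interaction a condition: "Both types of interaction (bio-bio and bio-social) should exist to form a syndemic".

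Statistical analysis, step four, says how interaction will be examined: "the synergistic (multiplicative) interactions between different latent constructs and measured variables will be tested using two-step estimation procedures". That sentence treats synergistic and multiplicative as the same thing. No additive-scale contrast appears anywhere in the section.

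The outcomes are events or dichotomies:
- **UK BioBank and NHANES:** "The syndemic outcomes are premature mortality and all-cause hospitalisation".
- **NHANES hospitalisation:** "All-cause hospitalisation data are based on being hospitalised in the year preceding the survey".
- **RELACHS:** "The syndemic outcome is self-reported health at phase 3 (very good, good versus fair, bad, very bad").

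The link function of the outcome equation is not given. For UK BioBank, the article does not say whether admissions are counted, timed or dichotomised.

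**The concern.** The hypothesis takes the sum of separate burdens as its benchmark, while the test takes the product. For a yes/no or time-to-event outcome under a log, logit, probit or hazard model, a zero product term means that effects add on the transformed scale. It does not mean that risks add. The same data can therefore meet the Introduction's definition and fail step four, or the reverse.

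This bears on the primary aim in all three datasets, because the interaction result decides whether a syndemic is declared. The secondary aim repeats the analysis by age, sex and ethnicity. Baseline risk is likely to differ between those strata, so the gap between the two scales would differ as well.

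**Working it through.** The article states no figure for the interaction test, so there is none to reproduce. The check uses two binary factors. Baseline risks and effect sizes are assumed, because the article gives none.

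**Notation.** p00 is the risk with neither factor, p10 and p01 the risk with one, p11 the risk with both.
- Expected joint risk under the sum: S = p10 + p01 − p00
- Interaction contrast: IC = p11 − S
- RERI = IC / p00
- Product OR at which risks exactly add: odds(S) / (odds(p00) × OR × OR)

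**Log link.** With single relative risks of 2 and 2 and no multiplicative interaction, the joint relative risk is 2 × 2 = 4. The sum gives 2 + 2 − 1 = 3. RERI is +1.00 while the multiplicative interaction is exactly null.

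**Logit link, worked case.** Take p00 = 0.05, OR 2 and 2, product term zero.
- Baseline odds = 0.05/0.95 = 0.0526
- p10 = p01 = 0.1053/1.1053 = 0.0952
- p11 = 0.2105/1.2105 = 0.1739
- S = 2 × 0.0952 − 0.05 = 0.1405
- IC = 0.0334, and RERI = 0.0334/0.05 = 0.67
- Product OR at exact additivity = (0.1405/0.8595)/0.2105 = 0.776

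A probit link with the same single-factor risks gives p11 = 0.165, still above 0.1405.

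**Logit link, other baselines, product term zero.**

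| p00 | OR for each | p11 | S | RERI | Product OR at additivity |
|---|---|---|---|---|---|
| 5% | 2 | 17.4% | 14.05% | +0.67 | 0.78 |
| 10% | 2 | 30.8% | 26.4% | +0.44 | 0.81 |
| 20% | 2 | 50.0% | 46.7% | +0.17 | 0.875 |
| 30% | 2 | 63.2% | 62.3% | +0.03 | 0.96 |
| 30% | 3 | 79.4% | 82.5% | −0.10 | 1.22 |
| 40% | 2 | 72.7% | 74.3% | −0.04 | 1.08 |

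In the first four rows, product ORs between the last column and 1.0 are super-additive but read as null or antagonistic. In the last two rows, product ORs between 1.0 and the last column are sub-additive but read as synergy. With equal odds ratios the two scales agree when the single-factor risk is 50%, for example 25% baseline with OR 3, or 40% with OR 1.5. For baseline risks of 3% to 10% and ORs of 1.5 to 3, the additivity threshold runs from 0.58 to 0.91.

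**Sample size does not help.** Take p00 = 5%, single relative risks 2 and 2, and joint relative risk 3.5. The joint risk is 17.5% against S = 15.0%, so RERI = +0.50, yet the ratio of odds ratios is 0.904 and the hazard-ratio ratio 0.889. With the 502,412 UK BioBank participants and assumed cell shares of 64/16/16/4%, z is about +8.1 for IC and −3.8 for the log odds ratio product term. The two scales would give firm and opposite answers.

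**Identity link.** Here the product term equals IC, and the mismatch disappears.

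**The case against.** Four counter-arguments deserve an answer.

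1. **Multiplicative may mean only a latent product term.** In a linear outcome equation that term does test departure from additivity. A condensed article may also leave the link to a fuller document. This stands as a limit on certainty. The point, however, does not rest on a missing link. It rests on two stated passages that use different benchmarks, and the product-term reading needs the authors to say so.

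2. **The Introduction asks for far more than the sum, so a multiplicative benchmark could be a deliberately stricter standard.** The article names no such threshold. Nor is a null product term a steady standard: with OR 2 on the logit link it corresponds to RERI of 0.79 at 3% baseline risk, 0.17 at 20% and −0.04 at 40%.

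3. **The Introduction names no risk scale.** That is true. Reading burden as risk is an interpretation, though a natural one for death, hospitalisation and poor health.

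4. **The low-risk examples may not suit these outcomes.** This stands. UK BioBank hospitalisation accrues over more than seven years, and RELACHS counts fair health among the poor outcomes. Baseline risks there may be well above 10%.

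A reader might infer that the error runs one way only, so that real synergy is missed and a positive product term can be trusted. The 30% and 40% rows of the table show that this fails at higher baseline risk. A reader might also carry the 5% figures over to all three datasets. Without event rates, the article does not support that.

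**Conclusion.** The point holds as a mismatch between the stated definition and the stated test. Under a log, logit, probit or hazard model, step four does not answer the Introduction's question, and the conclusion can be wrong in either direction. At low baseline risk, super-additive burdens may be called null or antagonistic. At high risk with sizeable effects, sub-additive burdens may be called synergistic.

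The size depends on link, baseline risk and effect size, none of which the article gives. In the illustrative logit cases the difference between the joint risk and the sum runs from +4.4 to −3.1 percentage points. The article does not show that any of the three analyses will in fact reach a wrong conclusion, and an identity-link outcome equation would remove the problem. The matter should be settled before analysis, because choosing the scale after seeing results could reverse the primary conclusion.

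**What to change.** In step four:
- State the outcome model and link for each outcome in each dataset. If an identity link is intended, say so. The product term then matches the definition.
- Otherwise, prespecify an additive-scale interaction contrast or RERI, computed from model-predicted risks at fixed levels of each construct, with delta-method or bootstrap intervals. Name it as the measure that answers the Introduction's definition.
- Report the product term alongside it.
- Assess both bio-bio and bio-social interactions, as the Introduction requires. The article gives no rule for combining several contrasts of each type, so any such rule would need its own justification.

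The cost is a few sentences of plan text, post-estimation code and computing time, chiefly for bootstrapping in UK BioBank. No new data are needed. With continuous latent constructs the contrast depends on the levels chosen, so those levels should be fixed in advance.

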**Figure 1 f1:**
[figure not shown]
Theoretical framework to test for syndemic interactions between social adversity and mental, physical and oral multimorbidity.

Oral diseases could be a key element in the above social adversity, mental and physical syndemic. They share the same social determinants and have bidirectional interactions with mental and physical conditions, precipitating and perpetuating their personal, social and economic impacts (1, 15). For example, the higher rates of oral diseases and conditions, such as dental caries, periodontal disease and tooth loss, and the increased risk of the late detection of oral cancer in people with mental disorders compared to the general population are alarming (16–18). Poor oral health affects simple daily functions such as eating, smiling and socialising, and increases social stigma and limited employment opportunities experienced by people with mental disorders (19–21). Oral conditions were the 3^rd^ most common reason for preventable hospital admissions in people living with severe mental illness (22). Indeed, people with mental disorders considered improving their oral health as part of bouncing back to normality (23).

Singer et al. underscored the importance of conducting further studies to explore new syndemics (8). Zahid et al. called for future studies to explore further specific potential syndemics involving mental disorders (24). No previous study has investigated the potential syndemic relationship between social adversity and mental, physical and oral multimorbidity (1, 25). Thus, the primary aim of the present work is to test for syndemic interactions between social adversity (socioeconomic adversity and traumatic events) and mental, physical and oral multimorbidity using the theoretical framework depicted in **Figure 1**. The secondary aim is to determine whether the syndemic relationships vary by age, sex and ethnicity.

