#### Design and study population

UK Biobank database comprises prospective biomedical data from 502,412 participants living across the UK and aged between 40 and 69 years at the time of recruitment (2006 to 2010). It benefits from data linkages to other health related records: primary care data, hospital admission data and cancer and death registries.

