### NHANES methods

#### Design and study population

The NHANES program is conducted in 2-year cycles by the Centers for Disease Control and Prevention. Data are obtained from self-reported questionnaires, clinical examinations and lab tests. Each cycle includes nearly 10,000 participants and is representative of the United States population across all age groups. In this project, NHANES cycles between 2009 and 2014 will be used due to required data availability and consistency. Attempts to harmonise variables’ selection across NHANES and UK BioBank databases are made.

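### The secondary question asks whether relationships differ between demographic groups, but the stratified analyses named to answer it include no test of the difference

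*Protocol article*

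**What the plan says.** The last paragraph of the protocol's Introduction sets the aim: "The secondary aim is to determine whether the syndemic relationships vary by age, sex and ethnicity". The research-question sections for UK BioBank, NHANES and RELACHS each repeat it, so it applies to all three datasets.

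The Statistical analysis section names the method for this question: "stratified analyses by age, sex and ethnicity will be performed". It says nothing more on the point.

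Two other parts of that section touch on these variables or on interaction:

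- Step two treats the three demographic variables as adjustment covariates: "a SEM to predict premature mortality and all-cause hospitalisation, controlling for age, sex and ethnicity, will be run".
- Step four tests interactions: "the synergistic (multiplicative) interactions between different latent constructs and measured variables will be tested using two-step estimation procedures". It is one of the steps listed for the question of whether syndemic relationships are present, and it is not linked to the demographic variables.

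**The concern.** Whether a relationship varies between groups is a statement about a difference between coefficients. Stratification gives a coefficient and a standard error in each group. It does not by itself give the difference, its interval or a test. The protocol names both the question and the method meant to answer it, and the method stops one step short.

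The gap matters because it leaves the comparison open to informal reading. The commonest informal reading, that an effect is present in one group and absent in another because only one reaches significance, fails in two directions:

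- With modest or unequal power, it suggests variation where there is none.
- With very large strata, where everything is significant, it hides variation that is real.

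Claims about differences by sex or ethnicity in any of the three datasets would then rest on no planned inference.

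**Working it through.** **Does another part of the plan supply the test?** Taking the Statistical analysis section in order:

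- Steps one to three concern indicators, the measurement model, direct and indirect paths, and fit. The factor-analytic work is to "reduce the number of indicators (observed variables) under each theoretical construct" and to show how items measure the constructs ("confirmatory factor analysis will be used to provide information on how indicator items measure underlying (latent) constructs"). Neither passage mentions groups.
- Step two adjusts for the demographic variables. Adjustment does not test modification.
- Step four is an interaction test, but it serves the primary question. Its reference to measured variables could in principle cover demographics, but the protocol assigns the variation question to stratification instead.
- No multi-group model, equality constraint, modifier product term or difference test is named.

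**How far can separate significance mislead?** The document gives no alpha, power, effect size or stratum size for this aim, so there is no stated figure to reproduce. What follows is an illustration.

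Assumptions: two independent strata, an identical true effect in both, each tested at two-sided 0.05, with powers a and b.

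P(exactly one significant) = a(1 − b) + b(1 − a)

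| Assumed powers | Calculation | Discordant |
|---|---|---|
| 50%, 50% | 0.50×0.50 + 0.50×0.50 | 50% |
| 80%, 80% | 0.80×0.20 + 0.80×0.20 | 32% |
| 90%, 90% | 0.90×0.10 + 0.90×0.10 | 18% |
| 99%, 99% | 0.99×0.01 + 0.99×0.01 | 2% (0.0198) |
| 95%, 30% | 0.95×0.70 + 0.30×0.05 | 68% |

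Unequal stratum sizes can be shown by fixing the overall power P and splitting the sample. With noncentrality 1.96 + z(P) and stratum share s, stratum power is Φ(noncentrality × √s − 1.96).

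| Overall power | 50:50 split | 80:20 split | 95:5 split |
|---|---|---|---|
| 80% | 50% | 61% | 73% |
| 90% | 47% | 63% | 80% |
| 99% | 24% | 52% | 83% |

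The entries are the chance of discordant significance when the true effects are the same.

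**The opposite error.** UK BioBank holds "prospective biomedical data from 502,412 participants living across the UK and aged between 40 and 69 years", so some strata will be very large. Suppose two strata have z = 12 and z = 6 with equal standard errors. Both are clearly significant, yet the test of their difference gives z = (12 − 6)/√2 = 4.24. Comparing significance alone would miss it.

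**What a direct test controls.** The statistic z = (b₁ − b₂)/√(SE₁² + SE₂²), or its Wald equivalent within an SEM, has its own false-positive rate: 5% per test at an assumed alpha of 0.05. That is a different quantity from the discordance rates above and is not a bound on them. It also accumulates. For three modifiers with one independent test each, 1 − 0.95³ = 14.3%. Several paths and three datasets would add more.

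**The case against.** The strongest reply is that a stratified SEM can be run as a multi-group SEM with equality constraints, which would contain the test. The text neither says nor excludes this. Even with separate fits, estimates and standard errors allow a difference test afterwards. This reply has force. A reader might infer that the groups will be fitted separately and compared only by eye, but the document does not say so. What stands is that no such test is planned in the text.

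Second, a reader might infer that variation will be declared when one stratum is significant and another is not. The protocol states no such rule, so the discordance figures describe a risk under assumed powers and do not predict what will be reported. For splits such as sex in UK BioBank, or in NHANES ("Each cycle includes nearly 10,000 participants"), power could be high. The 2% row shows that discordance is then rare, though the opposite error becomes relevant.

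Third, a reader might treat the absence of a measurement-invariance step, or of age cut-points, as errors in their own right. The document does not support that: these are specification details that a fuller plan could hold. In RELACHS, recruitment from two school years already supplies natural age groups. Both matters belong in the fix, because a valid comparison of latent paths needs them, but they are not separate defects.

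**Conclusion.** The point holds in a limited form. The protocol sets a question about differences between groups and names a method that, as written, yields within-group estimates and no inference on the difference. That conclusion rests on the text alone and needs no numerical assumption.

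The size of the possible harm does rest on assumptions: two independent strata, equal true effects, two-sided 0.05, assumed powers, and a reader who compares significance. On those terms, discordance runs from about 2% (99% power in each stratum) through 32% (80% in each) to 68% (95% and 30%), and to 83% for a 95:5 split at 99% overall power. The point affects the secondary aim in all three datasets and leaves the primary aim untouched.

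**What to change.** Replace the sentence on stratified analyses with a direct test of difference:

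- **Sex and ethnicity:** multi-group SEM with the same indicator set in each group. Hold loadings and thresholds equal where the data support it, with partial invariance if needed. Then use a Wald or scaled difference test of equality of the structural and interaction paths. Report each difference with its interval.
- **Age:** test it as a moderator, kept continuous where its range allows. In RELACHS, school-year group may serve.
- **Interpretation:** base any claim of variation on these tests, each at a stated alpha and with the number of tests acknowledged. Present stratum-specific estimates as descriptive.

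No new data are needed and the model family is unchanged. The work is real, however: group constraints must be combined with latent interactions, missing-data handling and, in NHANES and RELACHS, the survey design. Small ethnic groups may need merging, which should be specified before the analysis.
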